### **5.2.3 Blinding**

The ARV intervention will be open-label. In the proposed design, study subjects and physicians alike will be aware of the treatment assignment at the initiation of the intervention. The initiation of the intervention will occur between 2, and 4 weeks following initiation of standard anti-TB treatment. A placebo controlled design was not chosen because of ethical concerns and the sensitivities regarding placebo trials in the study population.

To address detection and reporting bias, we will use a reproducible, laboratory-based endpoint based on CD4+ measurements that is not subject to interpretation by investigators or subjects. Laboratory specimens will be identified by study subject ID numbers. Laboratory staff performing safety, microbiological and immunologic assays will be blinded to treatment arm assignment. Clinicians will be masked to treatment assignment during chest X-ray reading.

To minimize bias further, the frequency and duration of follow-up will be similar in both study arms. Outcome data will be collected and recorded in a standard manner for all study subjects. A Clinical Review Committee composed of senior level faculty at Case Western Reserve University, University California San Francisco, Makerere University review and classify all study outcomes (Table 6) in a blinded manner. Losses to follow-up will be recorded; reasons for the loss to follow-up will also be recorded. The potential bias from unbalanced treatments of intercurrent infections will be minimized by the use of a standard protocol for the treatment of these conditions.

### **5.2.4 Modified Directly Observed Therapy**

In this study, modified directly observed therapy (mDOT) will be used for both antituberculous and the punctuated ARV intervention. When medication is given by directly observed therapy, a health care provider, or designee, observes the patient swallow all pills and records that the dose was given. Directly observed therapy is an approach used to ensure adherence with study medication.

In this study, a team of home health visitors will deliver both the antituberculous and ARV treatment to study patients. The team of home visitors will be supervised by a single Ugandan medical officer. Home visitors will work with patients to determine a convenient time and place to deliver the medication Monday through Saturday. Home visitors will observe the patients swallow their pills six days a week. Thus, all antituberculous doses will be observed on these days and half of the punctuated ARV doses will be observed on these days because of the twice daily dosing. One day per week, patients will take their medication without medical supervision. Distribution of ARV medication will be strictly monitored to prevent misuse of study medication.

In the event that a patient defaults on a scheduled appointment with the home visitor, the home visitor will notify the study coordinator and begin to trace the patient.

The treatment supervisor will hold the patient’s anti-TB medications and treatment card. The patient and the treatment supervisor will both initial (or mark) the treatment card for each supervised dose63. The patient will initial (or mark) the treatment card for each unsupervised dose.

Before starting antiretroviral therapy, all patients will receive intensive counseling about antiretroviral therapy, especially ABC. They will be fully informed of the method of drug delivery through mDOT and will be counseled about the important of adherence with prescribed medication. They will be informed that unscheduled pill counts will be done to assess adherence to unsupervised doses.

As part of the mDOT, patients will be given verbal and written material about the toxicities associated with each medication including ABC. The educational material will give specific information about ABC HSR. This information will describe the early signs and symptoms of HSR and the risk of continuing with ABC in the face of these symptoms. Patients will be instructed to contact the study personnel using the 24 hour per day telephone service or present to the clinic immediately. The patients will be told that a study doctor will make the decision to stop the medication, but it is their responsibility to notify the study doctors of the signs and symptoms of ABC HSR. Patients will be instructed that they may not take ABC at any time in the future if ABC HSR occurs. This counseling will be done by study personnel who are fully knowledgeable about the risks of antiretroviral therapy, especially ABC. All patients will be given a card that indicates that they are receiving ABC as part of this study. The card contains instruction for how to reach a study doctor. It will also instruct health care providers to notify study personnel regarding the health of the patient.

## 5.3 Post Outcome – Step 3

During the study period, patients in Step 2 may develop a primary study outcome. If this event happens, the outcome will be confirmed and patients will be evaluated for safety of starting antiretroviral therapy. Patients who have experienced the main study outcome and who are eligible to start antiretroviral therapy will enter Step 3. For patients with a primary outcome but not eligible for antiretroviral therapy, because of contraindications to starting ARV treatment, they will remain in Step 2 and have the safety assessments repeated monthly or as clinically indicated until they are found eligible for antiretroviral treatment.

Patients will be assessed for the primary study outcome when CD4+ count falls below 250/ml or upon the development of a WHO stage IV AIDS-defining condition or a definitive diagnosis of a severe bacterial infection that meets WHO Stage 3 classification (Appendix II). To confirm the CD4 outcome, the CD4+ cell count will be repeated within 1 month after the initial measure below 250. If two measurements are <250 cells/L within a 3month time period, then the primary outcome has been confirmed. The outcome of an AIDS-defining condition must be confirmed by definitive or presumptive criteria (Appendix II). To confirm the outcome the following will be performed (see Appendix I, Step 3):

1. Medical history and physical examination, including weight
2. Adverse Event Survey
3. New diagnosis and hospitalization survey
4. Pregnancy test (urine or serum)
5. CD4+ lymphocyte count
6. CBC with differential
7. Liver function tests (AST and serum bilirubin)
8. Serum creatinine
9. Disease specific diagnostic test

These results will be valid for a period of two weeks and may be used for the safety evaluation, if within the acceptable range and time frame (2 weeks).

While the primary outcome is being confirmed patients will also be undergoing a pre-ARV safety assessment. If the evaluations below were not previously within the acceptable range or outside the two week time frame the evaluation that was not acceptable will be repeated. This ARV safety assessment may include results from the following (see Appendix I, Step 3):

1. Medical history and physical examination, including weight
2. Adverse Event Survey
3. New diagnosis and hospitalization survey
4. Pregnancy test (urine or serum)*
5. Complete blood count with differential
6. Liver function tests (AST and serum bilirubin)
7. Serum creatinine

**for those subjects that produce a positive pregnancy test see section 8.3 for specific ARV therapy assignment*

These results will be valid for a period of two weeks and will be used to determine whether there are any contraindications to starting antiretroviral therapy The following are relative contraindications to starting antiretroviral therapy for patients participating in this study (see section 4.4):

1. Fever > 38.0˚ C;
2. Weight < 40 Kg;
3. AST > 2.0 times upper limit of normal;
4. Creatinine > 2 mg/dL;
5. Hemoglobin < 9.5 g/dL;
6. Absolute neutrophil count < 1000 cells;
7. Current treatment with Ribavirin or Doxorubicin

Patients who have one or more of these contraindications to starting antiretroviral therapy will be evaluated and treated for the conditions causing abnormal values. Patients will be started on antiretroviral therapy once the acute condition has resolved. For patients who have persistent abnormal values that are attributed to progressive HIV infection, they will be eligible to start antiretroviral therapy with an appropriate regimen. Patients who are eligible to start antiretroviral therapy formally enter Step 3 and will have a pre-ARV baseline assessment, which includes (see Appendix I, Step 3):

1. HIV RNA Roche Amplicor
2. Quality of life assessment
3. Plasma storage
4. PBMC storage/ immune function (Flow cytometry to assess cell surface activation markers, EliSpot to assess CD4 and CD8 T cell specificity to HIV and microbial peptides, Whole blood assays to determine antigen specific response to HIV and microbial antigens)

Patients who satisfy all indications for therapy and safety evaluations will be started on ARV therapy. Once starting ARV treatment, patients will be followed per schedule of evaluations, Appendix I, Step 3.

If a patient is taking punctuated therapy at the time of a primary outcome, they will be evaluated for virologic failure (Section 8.1.3). Patients will be evaluated to determine whether a new protocol indicated regimen should be initiated or whether current regimen should be held, discontinued, or re-started. See section 5.2.1.4 and 8.1.4.

Patients who are not eligible for starting antiretroviral therapy at the time of the primary outcome will be reassessed in a month. If the contraindications for antiretroviral treatment have resolved, the patient will enter Step 3 as described above. If contraindications to antiretroviral treatment persist, then the patient will be followed and assessed for ARV safety eligibility monthly or as clinically indicated. Patients will be reassessed for contraindications at these monthly visits, or sooner if clinically indicated. If a patient is found eligible for antiretroviral therapy at any of these follow-up visits, then the patient will enter Step 3 as described above.

Patients will be started on self-administered ARV therapy in accordance with Ugandan National Treatment Guidelines, or as directed by the Principal Investigator or designee.

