### **5.2.1 Punctuated Antiretroviral Therapy**

#### **5.2.1.1 Drug Regimens, Administration and Duration**

Table 4. Study Intervention

| Study Arm | N | Intervention Period | Post-Outcome |
| --- | --- | --- | --- |
| Punctuated Therapy | 175 | 2RHZE/4RH QD + 6 Months ABC/3TC/ZDV (as Trizivir®) BID | Delayed antiretroviral therapy* |
| Delayed Therapy | 175 | 2RHZE/4RH QD | Delayed antiretroviral therapy* |
| *ARVs will be offered during study period to any patient when CD4+ count falls below 250/µL or when an AIDS-defining condition occurs. Patients who do not develop a primary study outcome during the study period will not be offered delayed ARV therapy. | | | |

Punctuated Therapy Arm:

Patients enrolled in the punctuated therapy arm will receive oral abacavir 300 mg/ lamivudine 150 mg/zidovudine 300 mg (as Trizivir®) twice daily with or without food. As each subject is enrolled, the study site must ensure that (1) the subject receives the **Trizivir**®warning card and medication guide, (2) the designated health care provider (e.g., physician, study nurse coordinator, or pharmacist) reviews the signs and symptoms of a hypersensitivity reaction (HSR) with the subject, and (3) the subject verbalizes an understanding of the steps to take in the event of a suspected HSR, including when and how to contact the study physicians. Study physicians will be available 24 hours per day through office or cellular telephone. Individual medication components of Trizivir®, will be available for dose adjustment.

For subjects who start Trizivir® but are found to be intolerant of it, alternative regimens will be available as described in Section 5.2.1.4, Antiretroviral Drug Substitutions and Replacements.

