This misattribution of the symptoms of HSR to another medical condition or delay in diagnosis of hypersensitivity has resulted in ABC being continued or reintroduced, leading to more severe or rapid (within hours) onset of HSR or death. Therefore, the diagnosis of HSR should be carefully considered for patients presenting with symptoms of these diseases, even if another medical diagnosis seems likely. Renal failure and anaphylaxis have also been reported in association with HSRs. Reintroduction of ABC in subjects after treatment interruption, with no preceding symptoms of HSR, has, rarely, resulted in HSR. Given the risk profile of ABC, ABC therapy SHOULD NOT be restarted following an HSR, because more severe symptoms will occur within hours and may include life-threatening hypotension and death. Subjects who develop signs or symptoms of hypersensitivity should discontinue treatment as soon as an HSR is first suspected and should seek medical evaluation immediately, preferably on the same day that symptoms are reported.

Physical findings may include lymphadenopathy and, occasionally, mucous membrane lesions (conjunctivitis and/or mouth ulceration) and hypotension. The rash is variable and may be absent, but often appears maculopapular or urticarial. Laboratory abnormalities that may accompany ABC hypersensitivity include elevated liver function tests (LFTs), creatine kinase, or creatinine or lymphopenia.

Symptoms related to this HSR worsen with continued therapy and usually resolve upon discontinuation of ABC. Restarting ABC following an HSR results in a prompt return of symptoms within hours. This recurrence of the HSR may be more severe than on initial presentation and may include life-threatening hypotension and death.

ABC HSR - *Diagnosis of HSR*

The clinical diagnosis of suspected HSR is described in Section 6.3.1.2.1. Hypersensitivity Reaction associated with Abacavir.

*ABC HSR - Management of HSR*

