The clinical presentation and severity of the HSR will dictate the supportive care offered to patients with HSR. In the most severe cases, patients will be hospitalized for 24 hours on the Tuberculosis Ward 5/6 of Mulago hospital for observation. Supportive care will be given and will include intravenous fluids for hypotension, treatment of alternative diagnoses, antipyretics, and symptomatic and/or supportive treatment as indicated. Although there are no clinical data demonstrating the benefit of antihistamines or corticosteroids in the management of hypersensitivity, they will be used in severe cases. In mild or moderate cases, without unstable vital signs, the medication will be stopped and the patient observed in the clinic for several hours. These patients will be taken home by home visitors and seen in follow-up the following day.

All clinical data obtained will be reported on the relevant case report forms (CRF), and the event “ABC hypersensitivity” is to be reported as a serious adverse event on the Division of AIDS, Regulatory Control Center Safety Office, SAE form. In addition, the **GlaxoSmithKline’s** “Abacavir Hypersensitivity Reaction Adverse Event Record” should be completed and returned to **GlaxoSmithKline** per the instructions on the form.

*ABC HSR - Fever*

The onset of fever may herald hypersensitivity. If HSR is suspected, then patients will be placed on the HSR Evaluation and Follow-up Protocol. In the event of a clinical presentation consistent with hypersensitivity, ABC should be held until evaluated by a study doctor, as described above.

*Toxicity Management for ABC/3TC/ZDV Tablets*

Should a subject experience toxicity resulting from the fixed dose combinations of ABC/3TC/ZDV or 3TC/ZDV, administer the individual formulations of ZDV 300 mg tablet, 3TC 150 mg tablet and/or ABC 300 mg tablet simultaneously and dose reduce or make protocol-allowed substitution(s), if necessary with permission from the protocol chairs. If a subject experiences an ABC HSR, discontinue ABC permanently.

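### Patient counselling on abacavir hypersensitivity (5.2.4) leaves out the hold-first rule set in 8.1.2.2.3 and 8.1.4.2.3

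*Protocol*

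**What the plan says.** Section 5.2.4 sets out what patients on punctuated therapy are told. They are taught the early signs of HSR and the danger of staying on abacavir once these appear. On what to do, the text reads: "Patients will be instructed to contact the study personnel using the 24 hour per day telephone service or present to the clinic immediately". They are then told that "a study doctor will make the decision to stop the medication, but it is their responsibility to notify the study doctors". Section 5.2.1.1 adds a warning card, a medication guide and a check that each participant "verbalizes an understanding of the steps to take in the event of a suspected HSR, including when and how to contact the study physicians".

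Section 8.1.2.2.3 orders the steps differently. Its background part says that subjects with signs or symptoms "should discontinue treatment as soon as an HSR is first suspected and should seek medical evaluation immediately". Its fever part says that, with a presentation consistent with hypersensitivity, "ABC should be held until evaluated by a study doctor, as described above". Section 8.1.4.2.3 instructs a patient who re-starts abacavir to hold it immediately if symptoms recur and to report to the clinic.

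On supervision, section 5.2.4 says that, Monday to Saturday, "half of the punctuated ARV doses will be observed on these days because of the twice daily dosing", and that "One day per week, patients will take their medication without medical supervision".

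A related clinician instruction stands in the management part of section 8.1.2.2.3. It lets on-site physicians continue abacavir in a suspected HSR if the signs are mild, or if they are attributed to another illness. Figure 4 in section 6.3.1.2.1 allows continuation only where another cause is likely and the patient can be followed closely.

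**The concern.** A patient who develops fever and rash at home has to decide about the next tablet before anyone has examined them. Section 5.2.4 is the text that prepares the patient for that moment. It assigns the stopping decision to the doctor and gives the patient the task of reporting. Sections 8.1.2.2.3 and 8.1.4.2.3 want the drug interrupted first and assessed second.

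The stake is patient safety. The protocol states that HSR has in rare cases been fatal, and section 8.1.2.2.3 warns: "Symptoms related to this HSR worsen with continued therapy and usually resolve upon discontinuation of ABC". Section 5.2.4 also counsels patients on the importance of adherence and tells them that unscheduled pill counts will check unsupervised doses. A patient left without a hold instruction is therefore inclined to take the next dose.

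**Working it through.** This is mainly a comparison of text; the protocol gives no figure to reproduce.

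**Order of events at first suspicion**

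| Section | Before the doctor's assessment | Addressed to |
|---|---|---|
| 5.2.4 | Telephone or come in at once; the doctor decides on stopping | Patient, first exposure |
| 8.1.2.2.3, background | Stop at first suspicion and seek evaluation | Subject |
| 8.1.2.2.3, fever | Abacavir held until evaluated | Not specified |
| 8.1.4.2.3, re-start | Hold immediately, then report | Patient, re-exposure |

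Three of the four put the interruption first. The exception is the counselling text for first exposure. That is the period that matters most: by section 6.3.1.2.1, HSR usually appears within the first 6 weeks, with a median onset of 11 days.

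**Can the texts be reconciled through the definitions?** Section 8.1.4.1 defines holding as temporary and discontinuing as permanent. If *stop* in 5.2.4 means permanent discontinuation, a patient could hold while waiting for the doctor's decision. Two things prevent this from closing the gap. Section 5.2.4 never mentions a hold, and section 8.1.4.2 gives even the decision to hold to medical officers, their supervisors and the investigators.

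**Unobserved doses (5.2.4)**
- Doses per week: 7 × 2 = 14.
- Observed: 6 days × 1 = 6.
- Unobserved: 14 − 6 = 8, and 8/14 = 57%. These are six second doses Monday to Saturday and two on the unsupervised day.
- Twice-daily dosing puts the next dose within about 12 hours.

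**Background incidence.** The protocol's 3% to 5% applied to 175 patients gives 0.03 × 175 = 5.3 and 0.05 × 175 = 8.8, so about 5 to 9 HSRs in the punctuated arm. This is the expected number of reactions, not the number affected by the wording.

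**Patients who might face the question without having HSR.** Section 6.3.1.2.1 says that HSR can be confused with rifampin effects, other HIV conditions and paradoxical reactions. Section 6.3.3 says that HSR and paradoxical reaction cannot be told apart. Section 8.1.2.2.8 puts paradoxical reactions at up to one third of treated patients, typically 1 to 3 weeks after starting antiretrovirals: 175/3 ≈ 58 at most. Not all of these would prompt a hold, so 58 is a ceiling for this one source.

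**The clinician instruction.** The *or* in the management part of 8.1.2.2.3 makes mildness enough by itself to consider continuing, which Figure 4 does not allow. The same paragraph requires prior consultation with senior investigators and stops abacavir if signs evolve or HSR cannot be excluded.

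**The case against.** The strongest reply is that the protocol already has the rule. Section 8.1.2.2.3 says to stop or hold before evaluation, and adds that where HSR is strongly suspected the patient is told to hold all antiretrovirals. Section 5.2.4 forbids none of this. It explains the danger of continuing and demands immediate contact, and a doctor can order a hold by telephone. Home visitors see patients six days a week, and the card and guide may well carry the hold instruction. Prompt contact followed by a physician's decision is also a defensible policy where symptoms are non-specific and re-starting carries its own risk.

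Much of this stands. It would be wrong to infer that the protocol is silent on what to do before evaluation; only the patient counselling omits it. It would also be wrong to infer that 5.2.4 tells patients to keep dosing. The safeguards make a long delay unlikely. What does not stand is the claim that the passages agree. If the intended policy were contact first and physician decision second, sections 8.1.2.2.3 and 8.1.4.2.3 would not put the hold first.

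On the clinician instruction, a reader might infer a second decision rule under which mild HSR continues on drug. The senior consultation and the override rule that out. The later passage that stops the drug in mild or moderate cases concerns supportive care for patients with HSR, so it does not directly contradict the instruction on symptoms still under evaluation.

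**Conclusion.** The inconsistency is real and confined to wording: the counselling in section 5.2.4 does not carry the protocol's own hold-first rule for suspected HSR. It should be corrected because the stated consequence of continuing can be severe and most doses are unobserved.

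Its size cannot be given as a number of patients. A reader might take the 5 to 9 expected reactions as the number put at risk by this wording. The documents do not support that, since nothing in them says how many patients would take another dose while waiting. Nor is there a threat to the trial's conclusions: the main analysis is as assigned (10.2.2.1), and the Clinical Review Committee classifies HSR for analysis (6.3.1.2.1).

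The conclusion rests on the protocol body. The wording of the warning card, the medication guide and the consent forms was not examined. If they already tell patients to hold, the practical gap is smaller, but 5.2.4 would still need to match them. The mismatch between the management part of 8.1.2.2.3 and Figure 4 is secondary.

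**What to change.** 1. **Section 5.2.4.** Replace the sentence on who decides with an instruction along these lines: if you have symptoms of a suspected reaction, hold Trizivir or any other abacavir-containing drug and contact the study doctor or come to the clinic immediately; the doctor will decide whether it is stopped for good or re-started.
2. **Section 8.1.4.2.** Note that patients may hold abacavir for suspected HSR pending evaluation, so that the allocation of decisions agrees with item 1.
3. **Warning card and medication guide (5.2.1.1).** Check that they say the same.
4. **Section 8.1.2.2.3, management, second paragraph (secondary).** Drop mildness as a ground for continuing and use the Figure 4 condition. Keep the senior consultation and the override unchanged.
5. **Optional.** In the background part of 8.1.2.2.3, change the verb for the patient's action from discontinue to hold, to match the definitions in 8.1.4.1.

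The drafting cost is small. The clinical cost is some additional short holds, which cannot be counted from the protocol and should not be assumed to be few, given the overlapping symptoms. Under section 8.1.4.2.3, re-starts are supervised and take place at Mulago Hospital. Section 8.1.2.2.3 also notes that reintroduction after an interruption has rarely caused HSR even without earlier symptoms. The protocol already accepts these costs by setting a hold-first rule elsewhere.
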